### Phase III

IM steps 4 and 5 will be completed in this phase in order to further modify the intervention, develop an implementation plan, and train two SWs from the study site on the modified intervention. IM step 4 (development of revised intervention) will entail using phase II findings to reexamine, and if necessary reconstruct, program objective tables developed in phase 1. This process will include CAB review of salient themes that emerged from phase II FGs and interviews, refinement of the program's logic model of change, and discussions about revising objectives, methods, and/or strategies. To ensure that modifications do not compromise intervention core elements, revisions will be presented and discussed with the second author (BD), the PCARE developer. The goal of this step is for the CAB to determine if intervention objectives and methods should be unchanged, deleted, revised, or added. Table 2 presents examples of possible modifications.

**Table 2 T2:** Examples of possible PCARE modifications

Sociocultural modifications		Provider-level modifications
Surface level	Deep level	
• Translate intervention materials into Spanish • Use bilingual care managers • Adapt community resource guide to Washington Heights	• Model interactions with medical providers and help patients formulate questions before medical visits • Reframe lifestyle change in terms of health, not thinness • Use health-related *fotonovelas* • Involve family members in decision making, as appropriate	• Add training session on CVD risk factors for SWs • Add training module for SWs on how to work effectively with PCPs • Distribute pocket cards to CMs and PCPs summarizing CVD risk factors

PCARE = primary care, access referral and evaluation; CVD = cardiovascular disease; SW = social worker; PCP = primary care provider; CM = care manager.

During IM step 5 (development of implementation plan), the CAB will formulate specific implementation objective tables and methods. In this step, the CAB will (a) discuss themes that emerged from phase II interviews and FGs regarding intervention acceptability, feasibility, and sustainability; (b) identify existing resources (*e.g.*, connections with primary care clinics) that facilitate intervention implementation; and (c) develop a performance objective table that links each implementation objective to the methods used to accomplish it. The goal is to write a detailed plan of what needs to be done to ensure the intervention is delivered at acceptable levels of fidelity and completeness. The plan will include CM tracking forms to log frequency, number, and types of patients' contacts and clinical services. These will serve as fidelity indicators for structural and clinical elements of the intervention [53].

Once the revised intervention is finalized, two SWs will be trained. Training will consist of four 90-minute education sessions that combine didactic presentations and interactive hands-on activities, such as role-playing, teach-back, and practice exercises. The training will be taught by intervention developers and other project consultants who are experts in primary care and cardiovascular care. The sessions will be based on the intervention materials, the American Heart Association guidelines for managing CVD risk factors [54], and the New York City Department of Health and Mental Hygiene continuing education modules that review existing guidelines for monitoring the physical health of adults with SMI [33]. Training topics include ascertainment of CVD risk factors; monitoring these risk factors in an SMI population; learning how to correctly obtain simple body composition measures (*e.g.*, weight, height), blood pressure assessment, and a basic medical history; developing patient education skills to boost patient recall and comprehension using teach-back techniques [55]; basics of motivational interviewing techniques; use of action plans [56]; and coordination with local medical care services. We will also develop and train SWs on how to follow specific clinical protocols to manage possible medical emergencies (*e.g.*, myocardial infarction, diabetic ketoacidosis) that require immediate attention by a medical provider (*e.g.*, clinic's nurse, emergency department). Lastly, during the pilot trial (see below) the two SWs will receive supervision every two weeks from the project primary care consultant, an experienced family physician, who will also provide clinical backup in case of medical emergencies. During these meetings, SWs will review patients' initial assessment and stated health goals and identify additional health needs, potential barriers to care, and strategies for ensuring receipt of services. An individualized patient report will be generated that identifies key medical issues, providers, and contacts, as well as short- and long-term goals. A copy of this report will be given to the patient, and if the patient consents, added to his/her medical records and given to his/her primary care provider.

### Phase IV

This phase will complete IM step 6 (evaluation) with a single group, pre-post, 12-month open pilot study (N = 30) carried out at WHCS. Two SW CMs will deliver the modified intervention, each carrying a caseload of 15 patients. Thirty adult Hispanic patients with SMI will be recruited. Inclusion and exclusion criteria are identical to those in phase IV. Based on the PCARE study recruitment rate of 69%, we will screen at least 45 patients to achieve our recruitment goal. A bilingual RA will recruit patients at WHCS through flyers, canvassing of waiting rooms, word of mouth, and provider referrals. We have allocated 18 months to this phase, which provides a six-month cushion for unanticipated problems with recruitment and attrition. Descriptions of the proposed measures for this study are presented in Table 3. As part of the planning process for this phase, the CAB will assess the appropriateness of these outcome measures for the intended patient population and, if necessary, identify other culturally relevant measures for key constructs (*e.g.*, acculturation, health literacy, illness perceptions).

**Table 3 T3:** Description of measures

Construct	Measure description
Feasibility	Study recruitment, assessment completion, and treatment attendance rates
Acceptability	CSQ and postintervention focus groups. The CSQ is an eight-item questionnaire scored on a four-point Likert-type scale. Scores range from 8 to 32, with higher score indicating higher satisfaction [68]. The CSQ is available in English and Spanish [69] and has excellent internal consistency in Hispanics [70].
Patient activation	PAM-13, [71] a 13-item scale that assesses patients' knowledge, skills, and confidence about self-management. Scores range from 0 (no activation) to 100 (high activation). PAM-13 has strong psychometric properties, including content and construct validity [71], has been tested across a range of chronic illnesses [72,73], and is available in English and Spanish.
Receipt of preventive primary care	PCARE study measure drawn from the USPSTF guidelines [74]. A total of 23 indicators are examined across four domains: (1) physical examinations, (2) screening tests, (3) vaccinations, and (4) education. Scored based on patients' medical records and self-report at baseline, three months, and six months. An aggregate preventive services score calculates the proportion of appropriate services obtained [18].
Health and mental health-related quality of life	SF-12 [75], a self-report measure available in English and Spanish and validated among adults with SMI that generates two summary scores for physical and mental health-related quality of life [76]. Summary scores range from 0 to 100, with higher scores reflecting better health.
Covariates	Demographics: *e.g.*, race/ethnicity, age, gender, education, and marital status Acculturation: nativity, language dominance, time in the United States, age of migration; the Bidimensional Acculturation Scale [77], a 24-item self-report measure that uses separate four-point scales to tap acculturation-related changes in two languages. Barriers to medical care: a list of 11 common factors that may prevent patients from seeking medical care [78,79]. Comorbid medical conditions: a list of 17 common medical conditions by patient self-report.

CSQ = Client Satisfaction Questionnaire; PAM-13 = Patient Activation Measure; PCARE = primary care, access and referral; USPSTF = U.S. Preventive Services Task Force; SF-12 = Short Form Health Survey; SMI = serious mental illness.

The primary outcomes of the pilot study are feasibility and acceptability. Two post-intervention FGs will be conducted with study participants to explore their reactions to the intervention. Each FG will be composed of 8-10 patients and follow the FG methods described in phase II. Although this is not an efficacy trial, we would be remiss in not taking this opportunity to initially explore the intervention's effect, as measured by patient activation, receipt of preventive primary care, and physical- and mental-health-related quality of life. Covariates include demographics, acculturation, barriers to care, and comorbid medical conditions. The RA will assess patients at baseline, 6 months, and 12 months. Self-report measures and medical chart abstractions will be obtained. Patients will be asked for consent to access medical records at WHCS and their primary care clinic. The RA will conduct these abstractions under [name]'s supervision.

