### Primary analysis

To evaluate feasibility, we will estimate recruitment rate, assessment completion rate, and treatment attendance rate by sample proportions and provide their standard errors based on binomial distribution. We will evaluate acceptability by assessing patient satisfaction (CSQ scores) repeatedly over time (baseline, 6 months, and 12 months). We will analyze improvement in patient satisfaction by a linear mixed-effects model with random subject-specific intercepts to handle correlation between repeated measurements of the outcomes. We will include time as predictor of interest. Significance of improvement in satisfaction over time will be assessed by testing whether the slope of time is zero.

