### Precision analysis

Since this is a pilot study for a future large randomized trial, we did not conduct a power analysis in accordance with recommendations in the new National Institutes of Health guidelines http://grants.nih.gov/grants/guide/pa-files/PAR-09-173.html and Kraemer and Kupfer [63]. Instead, we conducted precision analysis for the main study outcomes--feasibility and acceptability--by computing margin of error of an estimated rate to assess the precision that can be achieved by the proposed sample size. Margin of error is half the width of a confidence interval of an estimator. The smaller the margin of error, the tighter the confidence interval and the more precision we achieve for an estimator. We used the original PCARE [18] study treatment and completion assessment rates to estimate standard errors and margins of errors. PCARE's observed treatment completion rate was 0.68, with a sample size of 30, the standard error was 0.085 and the margin of error was 0.167. PCARE's observed assessment completion was 0.78 at 6 months and 0.69 at 12 months, the corresponding standard error is 0.076 and 0.084, respectively, and the margin of error is 0.15 and 0.17, respectively. For the CSQ scores (acceptability measure), when the standard deviation of the improvement of CSQ is 1, 2, or 4 points, the corresponding margin of error for estimating mean improvement is 0.18, 0.36, and 0.72, respectively. In all, our precision analysis indicates we have small margin of errors for each of our main study outcomes.

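### Table 3 scores receipt of preventive primary care at baseline, 3 and 6 months, but the pilot assesses patients at baseline, 6 and 12 months; the two schedules need to be reconciled

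*Protocol article*

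**What the plan says.** Phase IV describes a "single group, pre-post, 12-month open pilot study (N = 30) carried out at WHCS". Table 3, which that section introduces as describing the measures proposed for this study, has a row for receipt of preventive primary care: 23 indicators in four domains, summarised as the proportion of appropriate services obtained. The row fixes the timing as "Scored based on patients' medical records and self-report at baseline, three months, and six months".

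The Phase IV text after the table sets the assessment schedule: "The RA will assess patients at baseline, 6 months, and 12 months". It continues: "Self-report measures and medical chart abstractions will be obtained". The same paragraph names the outcomes by which the effect is to be explored, "as measured by patient activation, receipt of preventive primary care, and physical- and mental-health-related quality of life", so preventive care receipt falls within its scope.

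The Exploratory analysis section promises estimates with confidence intervals for these outcomes and names no time point. No section gives a separate schedule for preventive care receipt or explains why it should have one.

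**The concern.** The score draws partly on self-report, so each scoring time needs a patient contact. The Phase IV text schedules none at 3 months. Table 3 in turn gives this outcome no score at 12 months, the end of the pilot.

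A single-group pre-post study has no control arm, so its only effect contrast is follow-up against baseline. For preventive care receipt, the time of the last follow-up score depends on which part of the article is followed: month 6 under Table 3, month 12 under the Phase IV text. The background section reports that the parent PCARE trial doubled the rate of preventive care receipt, so readers are likely to look at this measure when judging whether the modified programme behaves similarly. Staff who work from the table and staff who work from the text would collect or score different data. Self-report not taken at the time cannot be fully recovered later.

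**Working it through.** No sample size, power or significance level rests on this point. The check is a comparison of the two schedules.

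**Step 1: the schedules side by side (months from baseline)**

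| Source | Data used | Months |
|---|---|---|
| Table 3, preventive care row | medical records and self-report | 0, 3, 6 |
| Phase IV text after Table 3 | self-report and chart abstraction | 0, 6, 12 |

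- In both: 0 and 6.
- Only in Table 3: 3.
- Only in the assessment schedule: 12.

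Of the two post-baseline scorings in Table 3, one (month 6) has a scheduled assessment and one (month 3) does not. Of the two post-baseline assessments in the text, one (month 12) has no score for this outcome under Table 3.

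**Step 2: whether another part of the article resolves the conflict**

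- *Primary analysis.* Satisfaction is measured "repeatedly over time (baseline, 6 months, and 12 months". This agrees with the Phase IV text but governs the satisfaction questionnaire only.
- *Other rows of Table 3.* None of them gives time points, so the timing of activation and quality of life comes from the Phase IV text alone.
- *Exploratory analysis.* No time point is named, so the section does not choose between the schedules.
- *Precision analysis.* It states that "PCARE's observed assessment completion was 0.78 at 6 months and 0.69 at 12 months". With N = 30, the standard error is √(p(1 − p)/30) and the margin of error is 1.96 times that:
  - p = 0.78: √(0.78 × 0.22/30) = 0.0756; 1.96 × 0.0756 = 0.148. The article gives 0.076 and 0.15.
  - p = 0.69: √(0.69 × 0.31/30) = 0.0844; 1.96 × 0.0844 = 0.165. The article gives 0.084 and 0.17.

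The article's figures reproduce. They show that precision was planned for 6- and 12-month completion, with no 3-month rate. The rates are the parent trial's, however, so they are planning inputs. They are consistent with the 0, 6, 12 schedule but do not set it.

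**Step 3: result**

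The sentence that directly contradicts Table 3 is the assessment schedule in the Phase IV text. The other sections agree with that sentence or are silent, and month 3 appears nowhere except the Table 3 row.

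**The case against.** **The row may describe the measure as the parent trial used it.** The row does call it a PCARE study measure. But the table is presented as describing this study's measures, and the only PCARE assessment times the article cites are 6 and 12 months. Nothing in the article ties a 3-month scoring to PCARE, so this reading does not remove the conflict.

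**Month 3 could be abstracted from the charts later.** That is true for the records part. It does not supply the self-report part, and it does not give a 12-month score.

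**A journal article condenses a fuller protocol.** That excuses omissions. Here the article states two schedules that cannot both be followed.

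**The outcome is exploratory.** This stands, and it limits the severity. The article says that the pilot is not an efficacy trial, and it plans only estimates with confidence intervals for this outcome. No primary conclusion or precision figure depends on it.

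Three stronger readings are tempting, and the article does not support them:

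- *A reader might infer that months 6 to 12 go unobserved for this outcome.* The Phase IV text has both data sources collected at 12 months. The contradiction is over which time points are scored, and 12-month data would exist if that text is followed.
- *A reader might infer that the planned triangulation fails.* The Phase V section describes integrating qualitative with quantitative findings and asking whether they converge. It does not require the quantitative outcomes to share time points.
- *A reader might infer that the look-back windows of the indicators are also wrong.* The article states no conflicting window, and scoring detail of that kind is commonly left to the full protocol or analysis plan.

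**Conclusion.** The inconsistency is real and its severity is moderate. It affects one time point on each side: a 3-month scoring whose self-report part has no planned assessment, and a 12-month assessment with no score for this outcome under Table 3. A pre-post comparison from baseline to 6 months remains possible either way, so what is in doubt is the 12-month value and the status of month 3. Recruitment, attendance, assessment completion and satisfaction are untouched.

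This rests on reading the Table 3 row as an instruction for this pilot, as the table's introduction says, and on the self-report part needing contact with the patient at each scoring time. Nothing suggests that a shorter follow-up was chosen on purpose for this measure. It is best treated as an internal inconsistency that has to be settled before data collection, because it decides whether a named effect outcome has an end-of-study value.

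**What to change.** In the preventive care row of Table 3, replace the stated time points with baseline, 6 months and 12 months, so that the row matches the assessment schedule in the Phase IV text.

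The cost is one line. No visit is added, because the 12-month self-report and chart abstraction are already planned, and no sample-size or precision figure changes.

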## Methods

### Setting

The Washington Heights Community Service (WHCS) of the New York State Psychiatric Institute will serve as the study site and community partner. WHCS is a state-run public mental health clinic located in the largest Hispanic community in New York state; its catchment area is approximately 74% Hispanic, mostly first-generation Dominican. About one-third of residents live in poverty, 31% lack health insurance, and 25% lack a regular medical home [46]. WHCS serves those members of the community that are most disenfranchised as a result of SMI. In 2008, WHCS had 1,030 patients, of whom 75% were Hispanics, 40% were male, and 90% had schizophrenia-spectrum or bipolar disorder. A study of 69 WHCS patients (78% Hispanic) revealed their poor health status [3]. Although 67% had had a physical exam over the past year, 89% of women and 59% of men were overweight/obese (body mass index > 25 kg/m^2^). Many had elevated rates of CVD risk factors: hypertension (29%), hyperlipidemia (22%), and diabetes (17%). The proposed modified CM program aims to help address these needs.

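### The pre-post change in preventive care may partly reflect better documentation, because the programme adds to the records that score it; baseline should be re-scored by service date

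*Protocol article*

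**What the plan says.** Phase IV is a "single group, pre-post, 12-month open pilot study (N = 30) carried out at WHCS". Table 3 defines receipt of preventive primary care as the share of appropriate services obtained: "A total of 23 indicators are examined across four domains", covering examinations, screening tests, vaccinations and education. The score has two sources: "Scored based on patients' medical records and self-report". On the records, the text adds: "Patients will be asked for consent to access medical records at WHCS and their primary care clinic".

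The programme acts on the same records. Under Care manager interventions, care managers link patients to primary care and coordinate between the two settings. Under Phase III, they are trained to take a basic medical history and body and blood pressure measurements. An individualized report is also produced: "A copy of this report will be given to the patient, and if the patient consents, added to his/her medical records"; with the same consent it goes to the primary care provider.

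The measure has two schedules. Table 3 reads "Scored based on patients' medical records and self-report at baseline, three months, and six months", while the Phase IV text reads "The RA will assess patients at baseline, 6 months, and 12 months".

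Phase IV names feasibility and acceptability as primary and this score as exploratory. The Exploratory analysis section plans average levels and rates with confidence intervals, and the Discussion says that the open design cannot test efficacy.

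**The concern.** A pre-post comparison in a single group is readable only if the outcome is captured equally well at both ends. Here the intervention is meant to improve the link between the mental health clinic and primary care. If it works, more records exist and they hold more history at follow-up than at baseline. Vaccinations and screening tests with long intervals are the most exposed: one done before enrolment may be absent from every source at baseline and then appear in a primary care chart first reached during the programme.

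A concurrent arm would not fully protect against this, but it would at least make the problem visible. With one group, more care and better documentation give the same rise in the score. The Discussion says that the pilot results will inform a more rigorous effectiveness trial, so an inflated change could be carried into that planning.

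**Working it through.** The article gives no baseline rate, standard deviation, target change or chart completeness for this score, so there is no stated figure to reproduce. What follows is illustrative.

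**Formula.** Let p be the true proportion of appropriate services received, held constant so that the programme has no effect on care. Let s0 and s1 be the probabilities that a received service is captured, by any source, at baseline and at follow-up. The expected scores are p × s0 and p × s1, so the spurious gain is p × (s1 − s0).

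**Inputs.** N = 30 and 23 indicators come from Phase IV and Table 3. All values of p, s0 and s1 are assumptions.

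| p | s0 | s1 | Baseline score | Follow-up score | Spurious gain | Of 23 indicators |
|---|---|---|---|---|---|---|
| 0.5 | 0.8 | 0.9 | 0.40 | 0.45 | 0.05 | 1.15 |
| 0.5 | 0.7 | 0.9 | 0.35 | 0.45 | 0.10 | 2.3 |
| 0.5 | 0.6 | 0.9 | 0.30 | 0.45 | 0.15 | 3.45 |

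The last column takes all 23 indicators as appropriate for the patient. At the edges of the assumed ranges, 0.3 × (0.95 − 0.90) = 0.015 and 0.7 × (0.9 − 0.6) = 0.21.

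**Effect of self-report.** Let r be record capture and q the share of unrecorded services that self-report recovers, so s = r + (1 − r) × q. With p = 0.5 and r rising from 0.6 to 0.9:

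- q = 0: 0.5 × (0.90 − 0.60) = 0.15
- q = 0.5: 0.5 × (0.95 − 0.80) = 0.075
- q = 0.8: 0.5 × (0.98 − 0.92) = 0.03
- q = 1: 0.5 × (1 − 1) = 0

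Self-report shrinks the artefact and removes it only if recall is complete.

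**A second illustration.** The Setting section says of catchment residents that "31% lack health insurance, and 25% lack a regular medical home". Suppose that 25% of trial patients lacked a usable primary care chart at baseline, that 40% of their appropriate services were truly up to date, and that half of these were missed by charts and self-report together at baseline but found later. The gain is 0.25 × 0.40 × 0.50 = 0.05. The low case is 0.25 × 0.30 × 0.30 = 0.0225 and the high case is 0.25 × 0.60 × 0.70 = 0.105, so about 2 to 11 points.

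**Against the available precision.** If an interval for the mean change were formed with N = 30 and an assumed standard deviation of change of 0.15 to 0.25, its 95% margin would be 1.96 × 0.15/√30 = 0.054 to 1.96 × 0.25/√30 = 0.089. An artefact of 0.10 alone would then put the interval above zero with probability of about 0.95 to 0.59.

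**After re-scoring by date.** If both windows are scored from the same final set of dated records, s1 = s0 for those services and p × (s1 − s0) = 0.

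**The case against.** The strongest objection is that the abstraction rule is not before us. An earlier service counts as improvement only if indicators are scored by when they appear in a chart, not by when they were performed. The article states neither rule, and look-back windows are commonly left to the full protocol. That stands as a limit: the absence of a printed rule is not the point. But a date rule applied visit by visit would not be enough, because a baseline scored only from the records available then cannot recover services found later. The baseline has to be re-scored at the end.

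Four stronger readings are tempting and are not supported.

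- A reader might infer that charts alone decide the score. Table 3 adds self-report, so an undocumented service can already count at baseline.
- A reader might infer that the care manager's report itself supplies the missing services. Its listed content is medical issues, providers, contacts and goals, not services received. The more likely routes are newly accessible primary care records and history taken by care managers. That the report prompts later self-report is conjecture.
- A reader might infer that the bias always favours the programme. The denominator is the number of appropriate services, and newly documented conditions could enlarge it and lower the score.
- A reader might take 25% as the share of trial patients without a chart. It describes catchment residents, and lacking a medical home is not the same as having no usable record. The Setting section reports that 67% of 69 WHCS patients had had a physical exam in the past year, and Patient focus groups says that cardiovascular risk factors are required content of patient records.

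The consequence is also limited: the outcome is exploratory, the Exploratory analysis section specifies no test of its change, and efficacy is disclaimed. The Discussion does not, however, name changing ascertainment as a limitation.

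**Conclusion.** The concern holds as a possible, mainly upward bias in one exploratory outcome. The documents establish the mechanism: one group, scoring that draws on charts, and a programme that connects patients to primary care and adds to those charts. They do not establish its size. The illustrations give about 2 to 10 or more percentage points (0.015 to 0.21 over the widest assumed ranges), and zero if self-report recall is complete. The upper part of that range is as large as the precision that 30 patients could give under the assumed standard deviations.

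Nothing here touches the primary feasibility and acceptability outcomes. The change is worth making because it is cheap and because the pre-post signal may feed the design of the later trial.

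**What to change.** 1. Reconcile the schedule of this measure between Table 3 and the Phase IV text, so that the last assessment is defined.
2. Record the date on which each service was performed.
3. At the last assessment, abstract all records then accessible, re-score the baseline and follow-up windows by service date, and use the re-scored baseline for the pre-post comparison. Scores made at each visit can be kept as a secondary description.
4. Do not count care manager entries alone as evidence that a service was received.
5. Report the record-based and self-report scores separately.

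The cost is a date field, slightly more abstraction work by the same research assistant under the same record consent, and one re-scoring. The apparent gain will probably be smaller. Re-scoring does not help with undated services, records that remain inaccessible at the end, or changes in recall, which is why the two sources should be shown apart.
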